### Study design

This is a Phase 3 clinical trial to establish safety and immunogenicity of a booster dose of licensed YF vaccine in children of different age groups, following primary immunization with the same vaccine at 9–10 months of age.

The proposed study leverages three well-characterized cohorts of infants, all of whom were vaccinated with the Institut Pasteur de Dakar 17D YF vaccine at 9–10 months of age within clinical trials run by the Vaccines & Immunity Theme in the MRC Unit The Gambia at the London School of Hygiene and Tropical Medicine (MRCG) over the last few years (
Figure 1). The databases of the previous trials, the YF PRNT
_50_ results from the primary immunisation and the stored samples are immediately available to the investigators. Consent for sample storage and future work on remaining samples was obtained at the time of initial recruitment.

**Figure 1. f1:**
[figure not shown]
Study design.

This trial will be conducted at one site: Fajikunda Health Centre in Fajara, The Gambia. Children previously enrolled in each of the three historic vaccine trials (summarised in
Table 1) will be recalled and invited for participation in the booster study. We will enrol until we have re-recruited 250 children per cohort. A roughly equal number of male and female participants will be enrolled in each cohort, but no absolute percentage figures will be set. Following individual sensitization and informed consent, basic clinical and anthropometric data will be collected, and children will have a pre-booster blood sample (5–10ml depending on age) taken for YF PRNT
_50_ (
Figure 1). All children will then receive a booster dose of a licensed 17D YF vaccine in use in The Gambia. All vaccines will be administered by the MRCG team. Local and systemic reactogenicity data will be solicited for 3 days. All children will then be invited back at day 28 (+/-7-day window) for a second blood sample (5–10 ml depending on age) and PBMC will be isolated and stored at the same timepoint (
Figure 1). If, based on initial laboratory work, it is determined that a smaller number of PBMC will be required at this timepoint, only serum will be collected for post-booster YF PRNT
_50_. A smaller cohort in each age group will be enrolled in the sub-study described below.

**
*Sub-studies*
**

In order to conduct systems biology investigations, which will provide novel insights into YF immune responses in children, subgroups of 30 children in each cohort will also be consented for a further sample (max. 5 ml) at either Day +7 for RNASeq or Day +14 for analysis of T cell responses (
Figure 1). The aim is to enrol the first 30 eligible children per cohort in the sub-studies, following consent provided on consent form version 1.0. Any child in these cohorts will have a maximum of 3 blood samples (up to 5 ml in the youngest age group, up to 10 ml/timepoint in the older age groups.)

### Laboratory investigations

**
*Humoral immune responses*
**

Serum collected pre and post YF vaccination will be separated from clotted whole blood samples, aliquoted and frozen at below -70°C prior to analysis at either the Institut Pasteur in Dakar or at the Robert Koch Institute in Berlin. This assay is not available in The Gambia. Post-primary serum from the primary studies is already available and safely stored for all participants and will also be analysed where data are not already available. Serum will be shipped using an IATA qualified shipping agent. A back-up sample will be retained at MRCG. YF neutralizing antibody titres will be determined by a validated PRNT assay and results provided to MRCG for subsequent analysis. The PRNT assay is conducted on a 96-well plate. The serum samples will first be inactivated at 60° Celsius for 20 minutes and then serial two-fold dilutions (from 1:10 to 1:20480) will be made. 30μL of the diluted serum samples will be added to the wells with 30μL of virus stock (containing 10
^3^ pfu/ml). The Institut Pasteur Yellow Fever 17D vaccine is used as the challenge strain for this PRNT and is titrated using serial dilution in a 24-well plate and through the observation of cytopathic effect in Porcine Stable (PS) kidney cells, measured as plaque-forming units (pfu). 30μL of cell culture medium will also be added to each well. Cell control, non-diluted virus and reference positive serum (National Institute for Biologicals Standards and Control) will be used as controls. The mixtures will then be incubated at 37° Celsius for 1 hour, after which another 6x10
^4^ PS cells will be added to each well. After 3–4 hours incubation at 37° Celsius, an overlay medium (0.6% carboxymethyl-cellulose in Fetal Bovine Serum (FBS)) will be added to each well and plates will be incubated at 37° Celsius for 3–4 days. Cytopathic effect will be observed using a standard microscope at x40 magnification. Subsequently, the medium will be removed, and the cells washed twice before 150μL of amido black (Sigma Aldrich) will be added to each well to stain and fix the cells to count the plaque-forming units. The PRNT90 and -50 antibody titres are defined as the last dilution that reduces the plaque forming units by 90% or 50% respectively when compared to the control. This YF PRNT assay has been optimised and validated
^
17
^.

**
*Cellular immune responses*
**

It is well established that both CD4 and CD8 T cell responses are elicited by YF vaccination
^
18
^, although their role in vaccine efficacy is not fully clarified. Recently published data in adults from a non-endemic setting have shown that both antibody and CD8 T cell responses might be impaired by a YF booster vaccine, compared to responses to the primary vaccine
^
18
^, however, there are no data in children.

This study provides an excellent opportunity to further understand the impact of a booster dose on cellular immunity and its relationship, if any, to neutralising YF antibody. In addition to antibody analyses prior and post YF booster vaccination and storage of PBMC, subgroups of children (n=30) in each study cohort will therefore be sampled either at D+7 for RNA sequencing or D+14 to study T cell adaptive responses.

**
*PBMC separation and storage*
**

PBMC will be isolated and stored. If, based on initial laboratory work, it is determined that a smaller number of PBMC will be required at this timepoint, serum will be collected alone. To separate the PBMCs, 3–5ml of blood will be collected in heparin tubes (BD Biosciences, CA, USA). The blood will be diluted using RPMI-1640, containing 100U/ml Penicillin and 100 µg/ml Streptomycin, together with 3% heat inactivated FBS (HI-FBS). This diluted blood will be layered over Lymphoprep at a ratio of 2:1 and then spun at 2400 rpm (1037g) for 30 minutes. The separated PBMCs will then be washed twice and resuspended in complete medium with 1% L-glutamine and 10% FBS. Cell counting will be performed using a Luna II automated cell counter (Logos Biosystems, South Korea). The cells will then be frozen in 10% DMSO in HI-FBS at -80°Celsius. After 48 hours, the cells will be moved to liquid nitrogen for further storage.

**
*Memory B cell assay*
**

To relate the serological responses to the B cell memory pool, memory B cell ELISpot assays will be carried out on fresh or banked PBMC from the V1 (baseline) and V2 (D+28) blood samples for all children where possible
^
19
^. Frozen PBMCs will be thawed and pre-incubated for 6 days with polyclonal antigen (stimulated PBMCs) or complete medium (unstimulated PBMCs). Stimulated and unstimulated cells will then be added to ELISpot plates, pre-coated with either 17D (to measure YF antigen-specific cells) or with anti-human IgG antibodies (to measure total IgG secretion). To allow direct comparison, PBMCs from the same subject, derived from visit 1 (day 0) and 2 (day 28) will be run on the same plate. Following incubation, biotinylated anti-human IgG will be added to detect antigen-specific and non-specific memory B cells. The addition of an alkaline phosphatase substrate creates insoluble coloured spots on the wells, which are enumerated using an automated ELISpot reader, with each spot corresponding to a single memory B cell.

**
*Flow cytometry and ExVivo staining for surface activation markers*
**

1x10
^6^ thawed PBMCs will first be washed in FACS buffer, which consists of PBS supplemented with 0.5mM EDTA and 3% HI-FBS (all Sigma-Aldrich, UK). The PBMCs will then be stained with the viability marker LIVE/DEAD™ (Invitrogen™) followed by surface staining using conjugated antibodies against CD3_V500, CD4_V450, CD8_FITC, CD38_APC R700 and HLA-DR_PE (all BD Bioscience). The cells will then be run on a BD Symphony™ Flow Cytometer and analysed using DB FACSDiva™ software
^
20
^ (open access alternative
^
21
^). Visits from the same participant will be run on the same plate and cohort samples will be distributed equally across plates to minimize batch effects. UltraComp eBeads™ (Invitrogen) will be used as controls. FCS files will be analysed using FlowJo
^
22
^ (TreeStar, USA). A template gating strategy, based on fluorescent minus one samples, will be used to analyse all FCS files.

**
*PBMC Restimulation and detection of activation markers*
**

1x10
^6^ thawed PBMCs will be stimulated for 18 hours with 5024 IU 17D antigen at 37°Celsius and under 5% CO
_2_. 1µg/ml SEB and R10 will be used as positive and negative controls, respectively. After the 18 hours, the cells will be stained with viability dye and the detection of surface markers will be performed, as above, using antibodies against CD3_V500, CD4_V450, and CD8_FITC (all BD Bioscience). After the surface staining, the samples will be fixed in 150µl of Cytofix/Cytoperm solution (BD Cytofix/Cytoperm™) for 15 minutes at 4°Celsius, after which the cells will be washed twice in Perm Wash buffer (BD Perm/Wash™). Intracellular staining will then be done using conjugated antibodies against CD154_APC-Cy7 (BioLegend
^®^), IL_2-APC (BioLegend
^®^), TNFα_AF700 (BD Bioscience), and IFNg_PE (BD Bioscience). Cells will then be incubated in the dark for 60 minutes at 4°Celsius. After a repeated washing in Perm Wash buffer, the cells will then be acquired through flow cytometry as described above. In addition to the template gating strategy, a Boolean gating analysis will be applied to identify T cell subsets expressing combinations of activation markers
^
23
^.

**
*RNA sequencing*
**

On Day 7, whole blood samples (1–2 ml) will be collected into PaxGene tubes and analysed using RNASeq methodology, recently established in the Gambia. It involves extraction of total RNA using the RiboPure RNA purification kit (Ambion ThermoFisher, Waltham, USA), followed by quantification and quality assessment using an Agilent 2100 Bioanalyzer (Santa Clara, USA). Polyadenylated RNA was captured and strand-specific cDNA libraries generated, which were subsequently sequenced using HiSeq 2500 (Illumina, San Diego, USA). This method was recently applied to small volume blood samples of an infant cohort to understand immune ontogeny in unprecedented detail
^
24
^ and will allow us to investigate whether YF antibody responses to the booster can be predicted by early “omic” signatures, as seen in adults
^
25
^. To date, this has not been studied in children.

All detailed “omic” and cellular immune studies can be implemented at the MRCG. Where possible, PBMC will be saved to test the hypothesis that the size of remaining B cell memory populations generated by primary YF immunisation will impact on the booster responses observed. The data generated will provide insights into the relationship between early innate responses, T cell activation, B cell profiles and functional antibody. We will use novel systems biology integrative approaches to inter-relate these immune-datasets, as we have recently published
^
24
^. As has been shown by us and others, systems biology approaches not only permit the observation of a global picture of vaccine-induced innate immune responses but can also be used to predict the magnitude of the subsequent adaptive immune response and uncover new correlates of vaccine efficacy
^
25
^. This approach has not yet been applied to understanding YF immunity in children and is an exploratory element of the trial.

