We have a unique opportunity to address these questions of timing and immunogenicity which are of public health importance. The proposed trial leverages three well-characterized cohorts of infants in The Gambia, all of whom were vaccinated with the Institut Pasteur de Dakar 17D YF vaccine at nine to 10 months of age within clinical trials run at the MRC Unit The Gambia at the London School of Hygiene and Tropical Medicine (MRCG). Details of the vaccine lots used and other metadata, including anthropometric measurements and other health indices related to the infants at the time of vaccination, are available. These trials were all conducted with ethical approval at the MRC Unit in The Gambia and already have consent for future use of data and stored samples in the original informed consent documentation. For most children in these cohorts, the initial serological responses to the vaccine are already documented from assays previously conducted at the Robert Koch Institute in Berlin, and for others, serum samples from 28 days following the primary immunization remain in secure -80°C storage. At the time of the proposed study, the cohorts will range in age from between 15 and 18 months, to between eight and nine years. These cohorts therefore provide a unique opportunity not only to examine antibody decline over this time period, but also to determine the optimal timing of a booster dose following infant priming. In addition, they allow for comprehensive immune-profiling of innate and cellular responses to YF vaccination in the different age groups to generate new insights into determinants of long-term immunity. Such data have never been generated in paediatric populations.

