### Study endpoints

Primary:

The primary endpoint of this study is the PRNT
_50_ titres post booster vaccination according to intervals between primary Yellow Fever vaccination and the booster dose.

Secondary:

The secondary endpoint is the rate of YF PRNT seroreversion (seropositive to seronegative) over a period of 9 months to 8 years following a single primary dose of YF vaccine administered to Gambian infants at nine months age.

Exploratory (Sub-study only):

Frequency of activated T cells, following re-stimulation with YF, in children of different ages following a booster dose of YF vaccinationLevels of YF specific memory B cells in children of different ages following a booster dose of YF vaccinationPossible impact of early innate responses, as measured by RNASeq, on antibody, B and T cell responses

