### Selection and withdrawal of participants

**
*Selection of participants*
**

The study will recruit 750 healthy children to receive the booster dose of YF vaccine. A roughly equal number of boys and girls will be recruited. We do not expect there to be differences in the results by sex.

Participants will be recruited/ re-approached from the previously enrolled participants in each of the vaccine trials listed in
Table 1 below.

**Table 1. T1:** Cohorts to be re-approached as part of the trial.

Dates of 9-month yellow fever vaccination	Age in January 2022	Number of infants	Co-administered vaccines in original study	Serology in primary study	Study reference
Jul 2013 – May 2014	8 years 6 years	~1504	Combinations of IPV and measles and rubella	PRNT _50_	NCT01847872 SCC1327
Feb 2018 – Aug 2018	4 years	~675	Measles and rubella, OPV and PCV	PRNT _50_	NCT03197376 SCC1517
Dec 2020 – May 2022	9 months	~320	Measles and rubella, OPV and PCV	PRNT _50_	NCT03606096 SCC1600

Upon screening, potentially eligible children will continue until the end of study unless the trial is stopped for some reason. A child may be excluded from the trial for the purposes of vaccination and/or clinical sampling or if ongoing participation is considered to be against their best interests or if a contraindication to vaccination and/or to the obtaining of clinical samples is identified. Such decisions will be made by the PI in discussion with other members of the clinical trial team and/or the sponsor. A child excluded in this way would be replaced and hence this would not alter the target sample size of 750. If not enough children from the previous cohorts are available, we will aim to recruit appropriate age groups from community health centres. We expect this to be an exception rather than the rule.

**
*Eligibility of participants*
**

Participants must meet all of the inclusion criteria and none of the exclusion criteria to be eligible to participate in the trial. A representative sample of children will be recruited from the target population.

Inclusion criteria:

Any child fitting the required age cohorts who has a documented record of having received a primary dose of the Institut Pasteur YF 17D vaccine between 9 and 12 months of age. Documented evidence can be either a previous record of YF vaccination with dates in our own trial registers if the child was a previous participant or has documented evidence on its Infant Welfare Card.

Exclusion criteria:

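### Seroreversion can compare carried-forward Berlin post-primary titres with pre-booster titres from another laboratory or a much later run, with no bridging stated, so an assay offset would read as waning or hide it

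*Protocol article*

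**What the plan says.** Under Study endpoints: "The secondary endpoint is the rate of YF PRNT seroreversion (seropositive to seronegative) over a period of 9 months to 8 years" after a single primary dose. This is a threshold crossing between two measurements on the same child, one taken 28 days after the primary dose and one taken just before the booster.

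The two measurements have different origins.

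- **Post-primary.** The Rationale says that for most children "the initial serological responses to the vaccine are already documented from assays previously conducted at the Robert Koch Institute in Berlin". Laboratory investigations adds that post-primary serum is "safely stored for all participants and will also be analysed where data are not already available". Existing results are thus carried forward, and only the gaps are filled by new assays.
- **Pre- and post-booster.** The same section has these sera separated and frozen "prior to analysis at either the Institut Pasteur in Dakar or at the Robert Koch Institute in Berlin".

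The section describes one PRNT procedure and calls it optimised and validated. It lists a reference positive serum among the controls and defines the titre as the last dilution in a two-fold series that reaches the required plaque reduction. It does not state that titres are converted to the reference serum, or that any sample is measured in both laboratories or in both the old and the new runs.

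**The concern.** A continuous comparison would absorb a laboratory offset as a shift in the mean. Seroreversion classifies each child against a fixed cut-off, so an offset moves children across the line. If the pre-booster laboratory or run reads lower than the historical one, children who kept their antibody are counted as having lost it. If it reads higher, real loss is hidden.

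The offset need not be the same in every cohort. Table 1 dates the primary vaccination of the oldest cohort to "Jul 2013 – May 2014" and of the youngest to "Dec 2020 – May 2022". If post-primary sera were assayed reasonably soon after collection, the gap between historical and current runs is years in the older cohorts and short in the youngest. Drift would then line up with interval since vaccination, the very axis along which the trial describes waning. Once the data are in, no analysis can separate the two without samples measured on both sides of the gap.

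**Working it through.** **Step 1: the plan's own figures.** With n = 250 per cohort, the Wilson interval for 90% is 85.7 to 93.1, as in Table 3. The other rows also reproduce, apart from one limit that differs by 0.1 through rounding. Two-sided power at alpha 0.05 for 85% against 75% is 0.80. The minimum power for any 15-point difference is 0.92. The stated precision and power hold, but they cover sampling error only.

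**Step 2: inputs for the offset.**

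- Pre-booster seronegative share: 22.2% + 7.5% = 29.7%, from the team's six-year data in the Background.
- One dilution step: 1 log2, from the two-fold series.
- Assumed, not in the documents: 95% seropositive after the primary dose, within-child correlation 0.5, log2 SD from 1.5 to 4.3, and the size of the offset.

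The upper SD comes from the same six-year data. If the detection limit lies one step below the cut-off (assumption), then SD = 1/(z(0.297) - z(0.222)) = 1/(-0.533 + 0.765) = 4.3.

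**Step 3: formula.** Let d be the pre-booster laboratory's offset in log2 units, negative when it reads lower. With standardised bivariate normal titres, a = z(0.05) = -1.645 and b = z(0.297) - d/SD:

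seroreversion = [Phi(b) - Phi2(a, b; 0.5)] / 0.95

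With d = 0: (0.297 - 0.0356)/0.95 = 27.5%.

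With SD = 2 and d = -1: b = -0.533 + 0.5 = -0.033, so (0.4868 - 0.0435)/0.95 = 46.7%.

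**Step 4: results.** Apparent seroreversion, with the change from 27.5% in brackets:

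| log2 SD | one step lower | half step lower | half step higher | one step higher |
|---|---|---|---|---|
| 1.5 | 53.5% (+25.9) | 40.0% (+12.4) | 17.3% (-10.2) | 9.9% (-17.6) |
| 2 | 46.7% (+19.2) | 36.7% (+9.2) | 19.6% (-7.9) | 13.2% (-14.3) |
| 2.5 | 42.6% (+15.1) | 34.8% (+7.3) | 21.1% (-6.4) | 15.6% (-11.9) |
| 3 | 40.0% (+12.4) | 33.5% (+6.0) | 22.1% (-5.4) | 17.3% (-10.2) |
| 4.3 | 36.0% (+8.5) | 31.6% (+4.1) | 23.7% (-3.9) | 20.1% (-7.4) |

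**Step 5: dependence on the other assumptions.** At SD 2.5, correlations from 0 to 0.7 change the result little: a one-step-lower reading gives 44.7% against a true 29.7% at correlation 0, and 42.0% against 26.6% at 0.7. The level of waning matters more. With only 5% seronegative before the booster, true seroreversion is 4.0% and a one-step offset gives 9.1% or 1.5%. An identical offset therefore distorts cohorts unequally.

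**Step 6: a check without the model.** In the six-year data, moving the cut-off from undetectable to 0.5 IU/mL changes the seronegative share by 7.5 points.

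**The case against.** **One laboratory may be used throughout.** The wording reads most naturally as a single laboratory still to be chosen. A reader might infer that children, visits or cohorts will be split between Dakar and Berlin; the text does not say so. If Berlin is chosen, the cross-laboratory risk disappears and only drift between runs remains. This stands, and it limits the point to what the plan allows.

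**The primary endpoint.** A reader might also infer that the between-cohort GMT ratios after the booster are biased. That endpoint uses only sera collected in this trial, so historical titres cannot touch it. It would be affected only if laboratory or batch tracked cohort, which the text does not state.

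**Magnitude.** Neither the SD nor the offset is documented. With an assumed SD of 2, a one-step offset would move 70% seropositivity to 51% or 85%; with SD 4.3 the same offset gives about 61% or 78%. Those figures also describe seropositivity at one visit, not seroreversion. Moreover, if the 22.2% with undetectable antibody truly have none, no upward offset makes them positive, and masking is capped at 7.5/0.95 = 7.9 points. Only a range is defensible.

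**Controls.** A validated procedure and a reference serum on each run make an uncorrected full-step offset a poor case rather than the expected one. They do not show that two laboratories, or runs years apart, read alike when no conversion to the reference is stated.

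**Detail left to other documents.** Plate layout and reporting unit can properly sit in a laboratory plan or SAP. For the memory B-cell ELISpot the article requires that cells from one child "derived from visit 1 (day 0) and 2 (day 28) will be run on the same plate". The lack of a matching PRNT rule is not itself a fault. What the article does fix is that old results are carried forward and that either laboratory may run the new sera.

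**Dates.** No assay dates are given. Long gaps are inferred from vaccination dates and fit the two older cohorts, not the youngest.

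**Conclusion.** The point holds for seroreversion. Followed as written, the plan can place the two ends of a child's comparison in different laboratories, or in runs separated by times that differ by cohort, with nothing stated that would allow the difference to be estimated.

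Under the stated assumptions, a one-step offset adds about 8.5 to 26 points of false waning or hides about 7 to 18, and a half step adds about 4 to 12 or hides about 4 to 10. The 10-point difference used for sizing falls inside the one-step range in both directions and at about the upper end of the half-step range. The masking figures shrink if undetectable children truly lack antibody. Whether any offset exists is unknown: this is a bias the plan permits, not one shown to be present. It concerns the children whose post-primary result is carried forward, and the documents do not support extending it to the primary post-booster comparison.

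**What to change.** In Laboratory investigations, under humoral immune responses:

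1. Replace the open choice with one named laboratory for all booster-trial sera not yet assayed, preferably the one that holds the post-primary results.
2. State that titres are expressed relative to the reference serum already included in the runs.
3. Retest a small random subset of stored post-primary sera from each cohort alongside the current runs. Use the old-to-new difference for a calibration sensitivity analysis of seroreversion, by cohort.

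The sample size does not change. The cost is a few extra assay runs and some stored serum. The Discussion says recruitment and follow-up are complete and sample analysis is under way, so naming a laboratory is cheap only for sera still to be run. For sera already assayed, the bridging subset and the calibration analysis are what remains affordable.
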